### Sample size {14}

The sample size is calculated according to the minimal difference recommendation for non-inferiority design [85]. The minimal important difference in the severity of insomnia is a decrease of eight scores on the ISI [84]. The non-inferiority margin is half the difference (4 points on ISI). Therefore, the treatment groups will be considered equivalent if their average ISI total scores do not differ by more than 4 points. Therefore, the study will detect the minimum clinically significant difference at a one-tailed test, 5% significance level, and 80% power. Finally, 64 participants will be required. Anticipation of 25% dropout rate, the required sample size was 80. To reach the desired sample size, the link for the study will be distributed and posted on online medical staff forums. Also, the trial information will be emailed to psychologist and psychiatrist to share the trial with their clients.

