### Data management {19}

The data will be collected via the Internet. The participants will complete the primary and secondary outcomes at three-time points: time 1: pretreatment to allocation, including baseline (week 1); time 2: immediately after the intervention, including post-treatment assessment (week 10), and time 3: 1-month follow-up (week 14). The data will be automatically coded and depersonalized and stored on a secure server. Before recruitment, the study protocol was designed with a concentrate on ensuring data quality through standardization of data collection processes. Data collection instruments were designed with validated items. Also, instrument guides were utilized as a reference for data collectors and supervisor, which included instructions for how to use instruments, definitions, and interpretation guidelines for each question. Also, all research team members received a comprehensive refresh course in the context of psychological assessments and ethics in clinical research. The supervisor ensure that each operation will be performed to a standard.

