## Statistical methods

### Statistical methods for primary and secondary outcomes {20a}

Main analyses will be conducted on the intent-to-treat (ITT) approach, including all randomly allocated participants, regardless of attendance. The last observation carried forward (LOCF) method is one way to handle missing data. In LOCF approach, the missing data are replaced by the last observed value of that variable. The time points for the observations of missed values will be reported. Descriptive statistics will be utilized to present the continuous variables as the means and SDs and categorical variables as the numbers and percentages.

To determine whether the IMBSR is inferior to ICBT-I, the confidence interval approach was used. Non-inferiority analysis will be assessed using an *F* test statistic generated from the linear mixed model and confidence intervals [86]. This tests whether the difference between the group means is statistically larger than the non-inferiority margin (clinically significant difference) and if the upper limit of the one-sided confidence interval of the difference between the group means is less than the pre-specified margin of non-inferiority. A non-inferiority margin of 4 points on ISI is chosen for the analysis. This means that the mean difference between the groups should not be more than 4 points in favor of ICBT-I, to establish noninferiority of IMBSR. Repeated-measures analyses of variance (ANOVAs) two (condition: iMBSR *vs*. iCBT-I) × three (time point: time1, time2, time3) will be designed to compare the main treatment effects of the conditions on secondary outcomes. The values of effect sizes are presented as partial eta squared and Cohen’s *d.*

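### The primary non-inferiority contrast names no adjustment for baseline ISI; making it baseline-adjusted would be a free gain in precision

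*Protocol article*

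**What the plan says.** All references are to the protocol article.

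- **Statistical methods {20a}**, model: "Non-inferiority analysis will be assessed using an *F* test statistic generated from the linear mixed model and confidence intervals". No fixed effects, covariates or response times are listed for this model.
- **Statistical methods {20a}**, decision rule: non-inferiority holds "if the upper limit of the one-sided confidence interval of the difference between the group means is less than the pre-specified margin of non-inferiority". The margin is fixed there: "A non-inferiority margin of 4 points on ISI is chosen for the analysis".
- **Sample size {14}** uses the same scale: "the treatment groups will be considered equivalent if their average ISI total scores do not differ by more than 4 points". The design is a "one-tailed test, 5% significance level, and 80% power", and the result is "Finally, 64 participants will be required".
- **Data management {19}** schedules the outcomes three times, the first being "time 1: pretreatment to allocation, including baseline (week 1"). Eligibility {10} also requires an ISI of at least 15, so a baseline value should exist for everyone randomised.
- **Randomization and masking {16a}** describes permuted blocks with 1:1 allocation and states no stratification factor.

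No section mentions adjustment for baseline ISI. None excludes it either.

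**The concern.** Baseline ISI is the same scale measured on the same person, so it is the obvious predictor of the post-treatment score. The written rule speaks only of a difference between group means, and naming a mixed model does not by itself bring baseline in. The only time structure the article spells out is the two-by-three ANOVA for secondary outcomes, where time 1 is an outcome level. If the primary model is built the same way, its post-treatment contrast makes no use of the baseline difference between arms.

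Two things are then at stake. The confidence limit that decides the trial is wider than it needs to be. And with no stated stratification and roughly 32 evaluable participants per arm, a chance difference in starting severity carries into the post-treatment means and can tip a result near the margin.

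**Working it through.** **Inputs from the article.** Margin 4; one-sided 5%; power 80%; 64 evaluable participants, so 32 per arm at 1:1; 80 randomised. **Assumed.** True difference 0; the SD, back-solved below; r from 0.2 to 0.5. The article gives neither the SD nor r.

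**1. The SD implied by 64.** The article states no SD, so 64 cannot be reproduced from its own inputs. Solving for it:

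SD = 4 / [(1.645 + 0.842) × √(2/32)] = 4 / (2.486 × 0.25) = 6.43.

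Putting 6.43 back into the usual formula returns 64 in total.

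**2. What an arm-by-time mixed model estimates.** I fitted a random-intercept model with arm, time and their interaction to simulated complete data on three visits, 32 per arm. The post-treatment arm contrast was 1.6605, and the raw difference in post-treatment means was also 1.6605. The arms differed by 0.41 points at baseline in that data set, and none of this was adjusted away. Last observation carried forward, which the article describes for missing data, completes the data and so creates the condition under which the two are equal. For anyone lost before the post-treatment assessment, the value carried forward is the baseline score itself.

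**3. Precision with adjustment.** Standard error = 6.43 × √(1 − r²) × √(2/32). Power = Φ(4/SE − 1.645). Half-width of the one-sided 95% limit = 1.645 × SE.

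| r | SE | Half-width | Power, 32 per arm | Power, 40 per arm |
|---|---|---|---|---|
| unadjusted | 1.609 | 2.65 | 80.0% | 87.2% |
| 0.2 | 1.576 | 2.59 | 81.4% | 88.3% |
| 0.3 | 1.535 | 2.52 | 83.2% | 89.8% |
| 0.4 | 1.474 | 2.43 | 85.7% | 91.7% |
| 0.5 | 1.393 | 2.29 | 89.0% | 94.1% |

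The 40-per-arm column applies if all 80 randomised participants enter the analysis and carrying values forward leaves the SD unchanged.

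**4. Validity and agreement.** In a simulation with 32 per arm and 20,000 trials per scenario, at r of 0.3 and 0.5:

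- True difference 4 (the margin): false non-inferiority was 5.0% and 4.9% unadjusted, 5.2% and 4.9% adjusted.
- True difference 0: power was 80.0% and 79.3% unadjusted, 82.6% and 87.8% adjusted. The two analyses gave different verdicts in about 7% and 13% of trials.

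**5. Size of the imbalance effect.** Chance baseline imbalance moves the raw difference with an SD of r × 6.43 × √(2/32), which is 0.48 points at r = 0.3 and 0.80 at r = 0.5, against a margin of 4.

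**6. Error rate given an observed imbalance.** For an imbalance of k standard errors in favour of iMBSR, the unadjusted rule's false non-inferiority rate at the margin is Φ[(−1.645 + rk)/√(1 − r²)].

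| k | r = 0.3 | r = 0.5 |
|---|---|---|
| +1 | 7.9% | 9.3% |
| −1 | 2.1% | 0.7% |
| +1.5 | 10.5% | 15.1% |
| −1.5 | 1.4% | 0.3% |

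The two directions offset each other, and the average over all randomisations is 5%, in line with step 4.

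**The case against.** The strongest reply is that the article nowhere calls the difference raw or unadjusted. It takes it from a linear mixed model, and a difference between group means is ordinary wording for a model-based estimate, adjusted or not. Baseline could be a covariate, a response with a common mean, or part of a change contrast. A change contrast has some textual support, since the objective is to reduce severity and the margin is derived from a fall of eight points. The covariate list of a named model is also something a condensed article may leave to the full plan. This stands to the extent that a reader may infer the primary analysis is unadjusted, but the document does not say so.

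It does not remove the point. The quantity compared with the margin is written out and repeated without a baseline term, and the model named delivers adjustment only if someone adds it. A simple change score is no substitute: at r = 0.3 its simulated power was 67.6%, against 82.6% adjusted.

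Two stronger readings fail:

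- **That the unadjusted rule declares non-inferiority too often.** Rates of 7.9% to 15.1% arise only when the imbalance favours iMBSR; the opposite imbalance gives 0.3% to 2.1%. Overall the error rate is about 5%.
- **That adjustment rescues a missed 80% power.** Power of 77.7% appears only with 30 observed per arm (80 less 25%). That shortfall comes from how the dropout allowance was calculated, which is a separate matter.

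**Conclusion.** The point holds as a free improvement to the stated primary contrast, not as an error that invalidates it. The article defines the decision quantity as a difference between group means and names no use of baseline ISI. Under the arm-by-time form of the model, on completed data, that quantity is the raw post-treatment difference. The comparison would be valid but less precise than the data allow.

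At 32 per arm the gain is from 80% to between 81% and 89% power for r of 0.2 to 0.5. If all 80 are analysed it is from 87% to between 88% and 94%. Requiring an ISI of at least 15 at entry narrows the baseline range, so the lower end is more plausible and the gain may be only 1 to 3 percentage points. The second benefit is that a fixed contrast removes a choice between two analyses that could disagree in roughly 7% to 13% of trials if there is no true difference (r of 0.3 to 0.5).

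These sizes rest on the back-solved SD of 6.43, the assumed r, a true difference of zero for power, and roughly normal data.

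**What to change.** In Statistical methods {20a}, define the quantity compared with 4 points as the baseline-ISI-adjusted difference, iMBSR minus iCBT-I, in mean ISI at the post-treatment assessment. Obtain it from the planned linear mixed model in one of two ways: with the post-treatment and follow-up scores as responses and baseline ISI, with its interaction with visit, as covariate; or with all three times as responses and a common baseline mean across arms. Compare its one-sided 95% upper limit with the margin, and report the unadjusted difference as supportive. If a fuller plan already specifies this, align the article's wording with it.

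The cost is one sentence, settled before unblinding, and one or two degrees of freedom. No extra participants, visits or data are needed, and the margin and sample size need not change.

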### Interim analyses {21b}

Not applicable as no ancillary studies are performed.

### Harms {22}

Despite few adverse effects that have been reported for the both interventions in many trials, the adverse effects in the study will be recorded and reported to sponsor and IRB. All intended and unintended results will also be published. The 24 h/7day phone number will be provided to report adverse effects. Participants will be told to feel free to contact us when needed.

### Dissemination plans {31a}

The study’s findings will be disseminated in publication with a double peer-reviewed policy. The dataset will be made available to academic investigators upon request from the corresponding author. Before a formal amendment to the protocol, any minor or major changes or modifications to the protocol which may lead to substantiate impacts on the study (i.e., study objectives, study design) or may affect on the benefit or safety of the participants or methodology (i.e., sample sizes) must be approved by the IRB. The template informed consent forms will be reviewed and approved by the IRB (see supplementary data).

### Plans, if any, for granting public access to the full protocol, participant-level dataset, and statistical code {31c}

No later than 1 year after the termination of the study, a completely de-identified deliver data set will be submitted to ISRCTN and publicly available.

## Discussion

The outbreak of COVID-19 is an emotionally challenging time, especially for nurses, and is associated with a range of mental and medical health problems with long-lasting effects. Although addressing the needs of front-line health care workers during the COVID-19 pandemic is a high priority, evidence-based evaluations and mental health interventions targeting front-line health care workers are relatively scarce. Special interventions to promote mental well-being in health care workers exposed to COVID-19 need to be immediately implemented, with nurses, and frontline workers requiring particular attention. Internet-delivered interventions can effectively prevent the progression of insomnia and improve comorbid symptoms and quality of life among nurses. It is expected that MBSR can effectively reduce insomnia symptoms. Individuals with depression experience deficits in mindful awareness of their emotions and experiences, particularly for nonjudgmental awareness and allowing oneself to notice emotions without triggering a repetitive negative thinking process such as rumination [87]. Mindfulness training is associated with decreased reliance on strategies such as rumination and over engagement and a more remarkable ability to tolerate negative emotions [88, 89]. It is expected that this study may address several gaps in the literature. Application of MBIs for insomnia may serve as a potential alternative or supplement to CBT-I.

The principal limitation of this present trial is the absence of placebo intervention. Additionally, although semi-structured insomnia interviews will be conducted to identify sleep disorders, patients are not screened for sleep apnea or periodic limb movement disorder. Additionally, with short-time follow-up, determining long-term effects will be difficult. Yoga has been shown to improve sleep. In this study, we do not have a plan to measure the difference between the effects of yoga exercises and IMBSR psychological exercises. Measuring the impact of each of these exercises can be considered in future studies.

## Conclusions

Despite limitations, the non-inferiority study design is a novel approach to evaluating whether a standardized, complementary treatment (i.e., MBSR) is as practical as a gold standard treatment rather than its potential benefits. This approach may lead to expanded evidence-based practice and improve patient access to effective treatments. Additionally, both interventions will be delivered through the Internet. Therefore, participants are not limited by environmental, geographical, medical, and mental issues, which will increase the generalizability of the results. Finally, establishing the ability of a standard manualized treatment such as MBSR to improve psychological distress and insomnia positively will increase available treatment options across healthcare workers and clinical nurses with insomnia. COVID-19 has limited availability of face-to-face interventions. While the application of the new technology in health settings was considered a far-reaching goal, the pandemic has acted as a catalyst to progress the use of the new technology in psychiatric settings. Consistent with this trend, treatment issues related geographical distribution of expert is now less divesting. Online CBT-I, electronically delivered intervention, and mobile health application course online represent a potential solution to overcome several of the barriers and could be a viable alternative method for mental health care delivery. The empirical studies suggest MBI can improve sleep quality in a diverse of clinical populations with sleep disturbance [90–93]. In addition to stress reduction, mindfulness-based interventions can also enhance nurses’ capacity for focused attention and concentration by increasing present moment awareness [94], while several evidence indicates that mindfulness meditation improved sleep quality compared with nonspecific active controls [95]. The study’s findings may provide greater confidence that the potential benefits of MBIs, which are not attributed to placebo effects commonly observed in usual care and waitlist controlled trials.

## Trial status

P**a**rticip**a**nt recruietment will be started on June 2022. It is expected that enrolment will continue until July 2022. Ethical approval for the study was obtained from the Research Ethics Committees of Lorestan University of Medical Sciences (reference number: IR.LUMS.REC.1399.269).

## Data Availability

Not applicable.

## Abbreviations

CBT: Cognitive behavioral therapy
CBT-I: Cognitive behavioral therapy for insomnia
COVID-19: Coronavirus disease 2019
CSQ-I: Client Satisfaction Questionnaire Adapted to Internet-Based Interventions
DBAS: Dysfunctional Beliefs and Attitudes about Sleep Scale Questionnaire
DSM: Diagnostic and Statistical Manual of Mental Disorders
FFMQ: Five Facet Mindfulness Questionnaire
HCWs: Healthcare workers
ISI: Insomnia Severity Index
ITT: Intent-to-treat
MBIs: Mindfulness-based interventions
MBSR: Mindfulness-based stress reduction
PHQ-9: Patient Health Questionnaire
RCT: Randomized controlled trial
SCID- IV –I: Structured Clinical Interview for DSM-IV Axis I Disorders
SPIRIT: Standard Protocol Items: Recommendations for Intervention Trials
